### Sample size and power analysis

Accepting an alpha risk of 0.05 and a beta risk of 0.20 in a two-sided test, at least 40 subjects in the sustained consumption study are necessary to recognize as statistically significant a difference greater than or equal to 10 units in the oxidized LDL. A dropout rate of 15 % was anticipated. This sample size will also permit to show, as statistically significant with a power of 80 %, a difference of 10 lag-time units among treatments in the clinical trial. Drop-outs before the first intervention period will be replaced in order to avoid drop-outs greater than 15 %. We will enlarge the sample size to 54 in order to have more statistical power for our results.

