### Statistical analyses

Normality of variables will be assessed by normal probability plots. One-factor ANOVA or Kruskal-Wallis test will be used to determine differences in basal characteristics and nutrient intake among the three olive oil interventions as appropriate. Period and sequence effects concerning a carryover effect will be assessed by means of an Analysis of Variance for repeated measures. The possible carryover effect will be corrected by the adjustment of final values after intervention periods by the values at the corresponding baseline period for each intervention. A general linear model for repeated measurements, with Tukey’s correction for multiple comparisons, will be fitted in order to assess differences between values at the beginning and at the end of each intervention period, and at postprandial state. Linear regression models will be used to adjust values at the end of the intervention periods for basal values in order to assess the linear trend across interventions. The paired comparison of post-intervention target concentrations will be carried out by a General Linear Mixed Model (GLMM) with the olive oil type (VOO, OHPCO, FOO) as fixed factor; individual level of test subjects as random effect; and, basal values for each intervention period, olive oil administration order, and age. Statistical significance was defined as *P* < 0.05 for a two-sided test. These statistical analyses will be performed using IBM SPSS Statistics 19.

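### The only named multiplicity correction sits on the start-to-end and postprandial analysis; the pairwise oil comparisons that bear on the hypothesis have none, giving about 12% family error per marker

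*Protocol article*

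**What the plan says.** Under Aim of the study, the hypothesis is an ordering of efficacy: the functional oil (FOO) above the optimized oil (OVOO), and OVOO above the standard oil (VOO).

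Statistical analyses then gives three routes to an efficacy result:

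- A repeated-measures general linear model with Tukey's correction which, in the article's words, "for multiple comparisons, will be fitted in order to assess differences between values at the beginning and at the end of each intervention period". The sentence goes on to include postprandial values.
- Linear regression on end-of-period values adjusted for baseline, to look for a trend over the three oils.
- A mixed model with oil type as fixed factor: "The paired comparison of post-intervention target concentrations will be carried out by a General Linear Mixed Model (GLMM"). No correction is named for it. The significance level for the whole section is two-sided P < 0.05.

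Under Intervention, each 3-week oil period follows a 2-week washout without olives or olive oil, with a sunflower product supplied instead.

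Sample size and power analysis opens with "Accepting an alpha risk of 0.05 and a beta risk of 0.20 in a two-sided test" and concludes that "at least 40 subjects in the sustained consumption study are necessary" to detect 10 units in oxidized LDL. It adds "A dropout rate of 15 % was anticipated" and then "We will enlarge the sample size to 54 in order to have more statistical power for our results". It gives no standard deviation and no allowance for multiple comparisons.

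**The concern.** The correction is placed where it does little for the trial's question. Within one oil, start against end is a two-level contrast, so there is no family of pairs for Tukey to protect. That contrast also compares the oil with the preceding washout, and any time trend is mixed in. It does not compare one olive oil with another.

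The three oil pairs (FOO–VOO, OVOO–VOO, FOO–OVOO) do form a family, and they are each tested at 0.05 without protection. Two things are at stake:

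- The chance of at least one false claim that two oils differ is well above 5% for every marker.
- Corrected within-oil tests sitting beside uncorrected between-oil tests invite the argument that FOO works better because its change is significant and VOO's is not. That is not evidence of a difference between the oils.

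**Working it through.** **Inputs.** Two-sided alpha 0.05, power 80%, at least 40 subjects, 10 units of oxidized LDL, 15% dropout and 54 enrolled, all from Sample size and power analysis. Three oils in a crossover give three pairs (Intervention). No SD is stated.

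**1. The plan's own figure.** Without an SD, 40 cannot be reproduced, only inverted.
- Normal formula, n = (SD_diff × (1.960 + 0.842) / 10)². With n = 40, SD_diff = 10 × √40 / 2.802 = 22.6 units.
- Paired t-test, n = 40, 80% power: standardised difference 0.454, so SD_diff = 10 / 0.454 = 22.0 units.

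**2. Family error as written.** If the oils do not differ, at least one of three pairwise tests is significant when the range of three standardised means exceeds 1.960 × √2 = 2.772. From the studentized range distribution (3 means, large sample), P = 0.122. Three independent tests would give 1 − 0.95³ = 0.143; the figure is lower because the pairs share oils.

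**3. Power if Tukey is moved to the oil pairs.** The critical value rises from 1.960 to q(0.95; 3)/√2 = 2.344 in large samples, or about 2.39 with the residual degrees of freedom at n = 40 (76).

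Let n₀ be the number of completers at which the unadjusted test has 80% power. By the normal formula, Tukey power at n completers is Φ(2.802 × √(n/n₀) − 2.344). The SD cancels.

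The article does not say whether 40 is before or after dropout, so both readings are shown: n₀ = 40, or n₀ = 40 × 0.85 = 34. Enrolling 54 with 15% dropout leaves 54 × 0.85 = 45.9, about 46.

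| Completers | n₀ = 40: normal | n₀ = 40: t-based | n₀ = 34: normal | n₀ = 34: t-based |
|---|---|---|---|---|
| 40 | Φ(0.458) = 67.6% | 68.5% | 75.6% | 76.9% |
| 46 | Φ(0.661) = 74.6% | 75.6% | Φ(0.915) = 82.0% | 83.3% |
| 54 | Φ(0.912) = 81.9% | 83.0% | Φ(1.188) = 88.2% | 89.4% |

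The t-based columns set the standardised difference from a paired t-test with 80% power at n₀ (0.454 for 40, 0.495 for 34). They then use the noncentral t with 2(n − 1) − 2 degrees of freedom and the Tukey critical value.

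With n₀ = 40, 80% power under Tukey needs 51 (t-based) or 52 (normal) completers. With n₀ = 34 it needs about 44 (normal).

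**The case against.** **The Tukey sentence can be read more kindly.** It also covers postprandial values, where repeated time points give a correction a real use. Because Tukey does nothing for a two-level contrast, the authors may have meant a model over oils and times. That is possible, but the sentence does not say so, and the model that does compare oils is described separately with no correction.

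**This is a condensed article, and an analysis plan may settle it.** If the article were merely silent on multiplicity, that would be a full answer. It is not silent: it fixes a correction and places it on contrasts that do not test the hypothesis.

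**Other safeguards exist.** The trend regression is a between-oil analysis suited to an ordering, and it should stay. Testing pairs only after a significant overall oil effect would also hold family error near 5% with three oils, but no such gate is stated.

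**A reader might infer that the power statement is wrong or that the trial is underpowered.** The document does not support that. The sample size assumes a single test at 0.05, which matches the uncorrected mixed model as written. The 68% figure arises only if Tukey is added, 40 means completers and only 40 complete, whereas 54 are to be enrolled and dropouts before the first period replaced. This part of the objection stands: power is a consequence of the chosen fix, not a second error.

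**Conclusion.** The point holds for the error rate. As written, the three between-oil comparisons are uncorrected and family error is about 12.2% per marker. This figure assumes no overall gate, equal precision for the three pairs and large-sample critical values. The within-oil tests, corrected or not, do not address whether the oils differ.

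The effect on power is conditional. If Tukey is moved to the oil pairs and about 46 complete, power is about 76% or about 83%, depending on whether 40 means completers or already includes dropout; if all 54 complete it is about 83% or more. These figures rest on the article's 80% claim being right at its stated size, which cannot be checked without the SD.

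Nor should 5% per marker be read as 5% for the trial. Many oxidation, inflammation and endothelial markers are listed as primary, and controlling the three pairs within each does nothing across them.

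**What to change.** Amend Statistical analyses as follows:

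1. Base efficacy conclusions on the between-oil comparisons: the mixed-model contrasts, with the planned linear-trend test kept as a between-oil analysis.
2. Control error across the three oil pairs for each marker, either by Tukey on the mixed-model contrasts or by a pre-specified testing order. The sponsor should choose the order. FOO against OVOO isolates the triterpenes, since Table 1 gives nearly equal total phenolics (487 and 490 ppm), so its place deserves thought.
3. Report start-to-end changes within each oil as descriptive.
4. Say that this control applies within a marker only.
5. State the SD behind the 40 and whether 40 is before or after dropout. If Tukey is used, restate power for the completers expected from 54.

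The cost is wording only; no extra subjects are required by the change itself. Under Tukey the stated power is somewhat lower than for a single uncorrected test. Under a fixed order the first comparison keeps the full 0.05, but later ones cannot be claimed once an earlier one fails.

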**Methods/design:**

A randomized, double-blind, crossover, controlled study will be conducted. Healthy volunteers (aged 20 to 50) will be randomized into one of three groups of daily raw olive oil consumption: VOO, OVOO, and FOO (30 mL/d). Olive oils will be administered over 3-week periods preceded by 2-week washout ones. The main outcomes will be markers of lipid and DNA oxidation, inflammation, and vascular damage. A bioavailability and dose-response study will be nested within this sustained- consumption one. It will be made up of 18 volunteers and be performed at two stages after a single dose of each olive oil. Endothelial function and nitric oxide will be assessed at baseline and at 4 h and 6 h after olive oil single dose ingestion.

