Urinary tyrosol and hydroxytyrosol		X	X	X	X	X	X	X
Plasma Triterpenes		X	X	X	X	X	X	X

**Table 3 Tab3:** Detailed study procedures in the bioavailability study (30 mL single dose)

Visit (V) number *IP, Intervention period*	Enrolment	V2 *(IP 1)*	V4 *(IP 2*)	V6 *(IP 3*)
Time Point, week	Up to -12	2	7	12
Informed consent form	X			
Randomization & allocation	X			
Treatment distribution		X	X	X
Blood collection at baseline (0 h) and at 30 min, 45 min, 1 h, 2 h, 4 h, 6 h, 8 h, 10 h, 12 h, and 24 h after oils ingestion		X	X	X
Urine collection at baseline (0 h) and at 0–2 h, 2–4 h, 4–6 h, 6–8 h, 8–10 h, 10–12 h, 12–24 h, after oils ingestion		X	X	X
Assessments				
*Primary outcomes*				
Urinary tyrosol and hydroxytyrosol at 0–2 h, 2–4 h, 4–6 h, 6–8 h, 8–10 h, 10–12 h, 12–24 h, after oils ingestion		X	X	X
Plasma Triterpenes at baseline (0 h) and at 30 min, 45 min, 1 h, 2 h, 4 h, 6 h, 8 h, 10 h, 12 h, and 24 h after oils ingestion		X	X	X
Endothelial function measurements at baseline (0 h) and at 4 h, and 6 h, after oils ingestion		X	X	X
*Secondary outcomes*				
Plasma gastrointestinal hormones t baseline (0 h) and at 2 h, 4 h, and 6 h, after oils ingestion		X	X	X

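### The repeated-measures general linear model named for start-versus-end and postprandial outcomes excludes, in its standard form, any volunteer with a missing reading; the mixed model already named in the same section would keep their data

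*Protocol article*

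**What the plan says.** The Statistical analyses section of the protocol article divides the outcomes between two classes of model.

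- Start-versus-end and postprandial outcomes go to one class, whose task is given as: "assess differences between values at the beginning and at the end of each intervention period, and at postprandial state". The article specifies that class in these words: "A general linear model for repeated measurements, with Tukey’s correction for multiple comparisons, will be fitted". Period and sequence effects are likewise given to a repeated-measures analysis of variance.
- End-of-period values compared between oils: "The paired comparison of post-intervention target concentrations will be carried out by a General Linear Mixed Model (GLMM"), with oil type as fixed factor and the participant as random effect.
- Software for all of this: "These statistical analyses will be performed using IBM SPSS Statistics 19".

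On the nested single-dose study, the abstract says: "It will be made up of 18 volunteers and be performed at two stages after a single dose of each olive oil". Table 3 lists three primary outcomes for it:

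- plasma triterpenes at 11 times;
- urinary tyrosol and hydroxytyrosol over 7 intervals;
- "Endothelial function measurements at baseline (0 h) and at 4 h, and 6 h, after oils ingestion".

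Each is taken after each of the three oils.

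On attrition, the Sample size and power analysis section says: "A dropout rate of 15 % was anticipated". Only people who leave before the first intervention period are replaced. The section on withdrawal and compliance adds that anyone with compliance of 80% or less counts as having dropped out.

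**The concern.** A general linear model for repeated measurements, in its standard form, holds one row per person with one column for each repeated reading. A person with an empty column leaves the analysis, along with every reading that was obtained. A mixed model fitted to one record per reading keeps whatever was observed. The section names both classes and gives the postprandial outcomes to the one that copes badly with gaps.

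This matters most in the single-dose study. It has only 18 people, each person contributes many readings, and it is the only place where endothelial function and the triterpene concentration curve are measured. A volunteer who completes two of the three oils is someone the plan itself should expect, yet that person has no place in an all-oil, one-row model. Complete-case deletion would throw away valid data, widen the intervals and let the result depend on who has a perfect record. In the sustained study, the before-and-after result and the between-oil result for the same marker could rest on different participants.

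**Working it through.** **The plan's own figures.** The article gives no sample size calculation for the 18-person study. The minimum of 40 for the sustained study cannot be rebuilt because no standard deviation is given. With the stated dropout, the enlarged sample gives 54 × 0.85 = 45.9, which is above 40.

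**Inputs from the article.** n = 18; dropout 15% (stated for the sustained study and carried over here); three oils. Readings per person at one stage of the single-dose study:

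- endothelial function: 3 × 3 = 9
- urinary tyrosol and hydroxytyrosol: 7 × 3 = 21
- plasma triterpenes: 11 × 3 = 33

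**Input assumed.** A share m of single samples is missing, independently of each other. The article gives no such rate, so 0%, 1% and 2% are shown.

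**Formula.** Expected complete rows = 18 × 0.85 × (1 − m)^k = 15.3 × (1 − m)^k, where k is the number of readings in the row.

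| Outcome and fit | k | m = 0% | m = 1% | m = 2% |
|---|---|---|---|---|
| Endothelial function, all oils in one model | 9 | 15.3 | 14.0 | 12.8 |
| Urinary phenols, all oils in one model | 21 | 15.3 | 12.4 | 10.0 |
| Triterpenes, all oils in one model | 33 | 15.3 | 11.0 | 7.9 |
| Endothelial function, one oil per model | 3 | 15.3 | 14.8 | 14.4 |
| Triterpenes, one oil per model | 11 | 15.3 | 13.7 | 12.3 |

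For example, triterpenes at 2%: 15.3 × 0.98^33 = 15.3 × 0.513 = 7.9. The per-oil rows are somewhat pessimistic, because a person who leaves late would still enter the fits for the oils already taken.

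**Where half of the 18 would be lost.** Solve 0.85 × (1 − m)^k = 0.5:

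- triterpenes (k = 33): m = 1.6%, or 2.1% without dropout
- endothelial function (k = 9): m = 5.7%

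**What a mixed model would use.** Suppose the 15% leave in equal parts during the three periods and lose the readings of the period in which they leave. The average number of people present per oil and time is then 18 × (0.95 + 0.90 + 0.85) / 3 = 16.2. With 2% of samples missing it is 16.2 × 0.98 = 15.9, whatever the value of k.

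**Start-versus-end in the sustained study.** With all six readings in one row, 45.9 × 0.98^6 = 40.7. With the two readings of one period, 45.9 × 0.98^2 = 44.1. At an assumed 3% the six-reading figure is 38.2.

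**The case against.** The strongest reply is that the complete-case rule is inferred. The article does not describe a one-row layout, does not say that incomplete people are excluded, and does not say that all oils and times enter one fit. Fitted per oil or per period, a gap removes a person from that fit only; fitted to one record per reading, it removes nobody. Missing-data rules also commonly sit in an analysis plan or full protocol, and neither is shown.

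Much of this stands, and it limits the size of the point. It does not remove it. The finding is not that a missing-data rule is absent. The article names a model class for these outcomes and, in the same section, a different class that handles gaps better. Per-oil fits are a weak escape, because the hypotheses in Aim of the study compare the oils with one another, and separate fits do not test that.

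Two stronger readings are tempting, and the documents support neither.

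- A reader might infer that most of the single-dose study would be lost. That needs all 33 triterpene readings in one model and a sample loss of about 1.6% or more, which the article does not state. Stated dropout alone leaves 15.3 of 18, and endothelial function keeps 12.8 at 2%.
- A reader might infer that the sustained study would fall below its minimum of 40. At 2% even the six-reading row gives 40.7. The 38.2 needs both an assumed 3% and all six readings in one row. The article does not tie the 40 to the before-and-after analysis, and it describes the companion lag-time difference as one between treatments. The end-of-period comparison between oils uses the mixed model and is not touched.

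A further fair objection concerns the remedy. Random effects for participant, or participant and period, imply equal correlation among all 11 samples from 0 to 24 h. That is doubtful for a concentration curve, and a richer structure is hard to estimate in 18 people.

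**Conclusion.** The point holds in a limited form. The named model is a poor choice for the start-versus-end and postprandial outcomes, including the Table 3 primary outcomes, because in its standard form it discards partial data that the plan has reason to expect.

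On the stated dropout alone the loss is modest: about 2.7 of 18 volunteers (18 − 15.3) and whatever readings they had given. Beyond that, the size depends on two things the article does not fix: the rate of missing samples, and whether all oils and times share one model. Under one model and 1% to 2% sample loss, endothelial function is reduced moderately (14.0 to 12.8 complete rows) and the triterpene profile substantially (11.0 to 7.9). These figures cover one stage of the single-dose study and assume that gaps occur independently. The plan should be changed on this point, but the main between-oil comparison is sound in this respect.

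**What to change.** In Statistical analyses, extend the mixed model already named to the start-versus-end and postprandial outcomes:

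- Fixed effects: oil, time, oil × time, period and sequence. Random effect: participant. Use all available readings.
- For the postprandial curves, pre-specify a within-period covariance that allows for serial correlation, such as first-order autoregressive or spatial power, with a small-sample degrees-of-freedom correction. The sampling times are unevenly spaced (from 15 minutes to 12 hours apart), which favours a structure based on actual time. Confirm that the named software version offers the structure chosen. Alternatively, model one summary per oil, such as AUC, and state how AUC is obtained when a sample is missing.
- State how this analysis set fits with the rule that compliance of 80% or less counts as dropout.

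The cost is wording. No new data or visits are needed, and a mixed model is already planned in the same software. The real downside is that a covariance structure must be chosen with only 18 people to support it, so it should be simple and fixed before unblinding.

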## Discussion

The NUTRAOLEUM Study is designed to assess whether, besides an increase in the polyphenol content of the olive oil (OVOO), and additional enrichment of this OVOO with oleanolic and maslinic acids from olive seeds (Functional OO, FOO) will increase the healthy benefits of these OOs versus an standard VOO. The benefits of rich-phenolic natural OOs on risk factors for chronic diseases have been established in human studies Diet [1]. Within the PREDIMED (Prevención por Dieta Mediterránea) Study we observed a decrease in the atrial fibrillation in cardiovascular disease risk individuals (n = 7440) when the Mediterranean diet was supplemented with extra-VOO [21]. The EUROLIVE Study was a randomized, crossover, controlled study with 200 European healthy volunteers, and three similar OOs but with differences in their phenolic content (from 2.7 to 360 ppm) [22]. From our EUROLIVE results an increase in HDL cholesterol and a decrease in the oxidative damage to lipids, including the *in vivo* oxidized LDL a recognized biomarker for CHD [23], in a dose-dependent manner of the phenolic content of the OO administered were observed. Recently in a subsample of the EUROLIVE study we have reported: 1) an increase of the HDL functionality, evidenced by an increase in the cholesterol efflux from cells, linked to the high-phenolic content OO versus the low content one [24]; and 2) a decrease in total and small LDL particles [25]. Total LDL particles (LDL-P) is now considered to be a biomarker for CHD with the same or higher predictive power than LDL cholesterol [26]. Benefits of high phenolic VOO consumption on other risk factors particularly inflammation, endothelial function and thrombosis markers have also been reported *in vivo* in humans, including a nutrigenomic effect modulating atherosclerosis-related genes towards a protective mode [1, 27]. In front of other edible oils, VOO reduced the postprandial endoplasmic reticulum stress in obese people [28].

In our experience, functional olive oils enriched with phenolic compounds provide more health benefits than the parental VOOs. A functional olive oil enriched with its phenolics (990 ppm), when comparing with the parental VOO (200 ppm of phenolic compounds), was able to reduce the endothelial dysfunction [29] and to enhance the expression of cholesterol efflux related genes in *vivo* in pre- and stage 1 hypertensive patients [30]. Within the VOHF (Virgin Olive oil and HDL Functionality) Study we have recently reported that a functional olive oil enriched with OO phenolics (500 ppm) and with them and those of thyme (500 ppm equimolar) improved the lipoprotein particle subclasses distribution and their associated atherogenic ratios [31, 32]. The functional OOs used in the studies referred to above were enriched from isolated OO phenolic extracts. In the NUTRAOLEOUM study, however, a “coupage” of natural olive varieties together with selected extraction procedures were used for making the OVOO. Besides a more equilibrate micro-nutrient composition, the organoleptic characteristic profile, corresponding to a natural VOO, is expected to enhance the consumers acceptation of the NUTRAOLEOUM OOVO.

The NUTRAOLEUM Study will also evidence for the first time whether the OO triterpenes can provide benefits for human health. Despite a large body of experimental data reporting bioactive effects [4–6], at present, and to the best of our knowledge, no human randomized controlled trial for assessing the *in vivo* potential benefits in humans of oleanolic and maslinic acid from olive oil has been undertaken. We are aimed to take the challenge on the issue in order to provide first level evidence whether triterpenes from olive oil have, or have not, bioactivity *in vivo* in humans. Data on the bioavailability of oleanolic and maslinic acid in humans are scarce. The NUTRAOLEUM Study will provide for the first time information from a randomized controlled trial on the bioavailability and disposition in humans of the oleanolic and maslinic acids present in OOs. Olive oil, a recognized healthy food, can not be consumed in great quantities. Due to this, an increase in the OO bioactive components, such as triterpenes (i.e. FOO) and phenolic compounds (i.e. both FOO and OVOO) is a way for enhancing OO health-promoting properties whilst consuming the same or less fat. Currently, functional foods are developed to improve the properties of natural food components. However, functional foods must be tested in human clinical intervention trials with an appropriate design. Consumers are more and more frequently asking for an “added value” in the nutritional properties of the food to be purchased. Thus, answers from the Olive Oil Industry and from researchers, concerning functional olive oils with tested healthy properties are needed.
